#### Life Flex Program and Low-Intensity Therapist Assistance

Participants who are *stepped up* to the low-intensity therapist-assisted treatment condition will complete the same dMH treatment program (Life Flex), with the addition of a 10-minute weekly video chat session with a therapist for support and progress check-in of program content. The role of the therapist in the low-intensity treatment condition is to support the participant’s engagement with the Life Flex program by specifically checking participant progress with modules, task reinforcement, providing clarification where required, encouraging reading and skill practice, and ensuring that participants are clear about their between-session module tasks assigned for completion.

#### Life Flex Program and High-Intensity Therapist Assistance

Participants who are *stepped up* to the high-intensity therapist-assisted treatment condition will complete the same dMH treatment program (Life Flex), with the addition of a 50-minute weekly video chat therapy session with a therapist for individualized tailoring of the program content. Participants in the high-intensity treatment condition will have the opportunity to receive therapist guidance, tailored program content, questionnaire feedback, and support for generalizing skills to daily life and to engage in problem-solving where required.

Therapist assistance in both low-intensity and high-intensity conditions will be offered to participants for a period of up to 7 sessions. To ensure treatment fidelity and standardized treatment, the therapists will be provided with a treatment manual, with random checks of their recorded video chat sessions (eg, 20% of the total) by independent raters to determine adherence to the study protocol and treatment fidelity.

### Assessors and Therapists

#### Therapist Training Program

Before commencement of the trial, provisionally and generally registered psychologists will be required to complete and obtain competency in a purposively developed 14-hour, 5-module web-based training program covering an introduction to dMH interventions (specifically video chat technology), diagnostic assessments (covering MINI, anxiety, depressive disorders, and suicidality), qualitative interviewing techniques, and transdiagnostic cognitive behavior therapy principles that underpin the Life Flex dMH treatment program. The training program comprises a 40-item multiple-choice competency assessment, for which therapists are required to obtain a minimum score of 80%. The training program also contains a pre-evaluation and postevaluation survey designed to assess therapists’ knowledge about and confidence in the use of dMH interventions before and upon completion of the program and to obtain their satisfaction ratings of the training program.

#### Outcome Assessors and Trial Therapists

The assessors who complete the diagnostic clinical assessments and the therapists who deliver the low-intensity and high-intensity treatment assistance will be provisionally and generally registered psychologists who are on clinical placement at the Federation Community Psychology Services at Federation University in Ballarat, Victoria, Australia. A new assessor will be assigned for all 3 assessment time points and will differ from any therapist assigned to participants in both the low-intensity and high-intensity therapist-assisted conditions. The assessors will complete and be required to demonstrate competency in diagnostic assessments before administration, and both assessors and therapists will receive training and supervision from an experienced clinical psychologist throughout the trial.

Both assessment and therapist sessions will be audio or video recorded (with participants’ permission), so that random checking (eg, 20% of the total) can be completed to ensure adherence to administration, to enable agreement and interrater reliability of diagnoses, and to ensure that adherence to the therapist’s role (low or high intensity) is maintained. Adapted versions of the Internet-Delivered Cognitive Behavior Therapy–Therapist Rating Scale [25] and Cognitive Therapy Rating Scale (Multimedia Appendix 2) will be used by supervisors in the review process to ensure treatment fidelity in both treatment conditions. Each therapist will also be required to undertake regular supervision, where any remedial strategies to improve fidelity will be implemented. Remedial strategies will include the provision of constructive feedback, review of the components of treatment in sequence, further practice of skills where drift may have occurred, additional training (if necessary), review of initial fidelity training materials, and extra coaching or supervision.

#### Participant Interviews

Within the study, there will be 4 different types of interviews offered to participants depending on what is relevant to them: exploration of experiences of assessment via video chat technology, exploration of experiences of therapist assistance delivered via video chat technology, exploration of reasons for nonengagement with therapist assistance, and exploration of reasons for disengagement and withdrawal. Participants will be offered an interview at a suitable time and via their preferred mode: instant message, telephone, video chat, or email. Participants will also have the option to complete a brief exit survey instead of an interview if they withdraw from the study or choose not to engage with the offer of therapist assistance.

Participants who complete a diagnostic assessment or receive at least two therapist-assisted sessions via video chat will be invited to participate in a semistructured interview to reflect upon and share their experiences with the video chat interaction. They will be asked a series of questions focusing on their ability to develop a therapeutic alliance with their assessor and therapist, their views on video chat technology, exploration of any technological issues experienced, and overall strengths and limitations of video chat. The interviews will be conducted by the first author, focusing on asking questions in an open, curious, and reflective manner. If the interview is completed via telephone or video chat, it will be audio recorded (with participants’ permission) for qualitative analysis.

#### Assessor and Therapist Interviews

The provisionally and generally registered psychologists of the study will also be invited for interview to share their experiences with administering diagnostic assessments and delivering treatment via video chat technology and explore their training experiences. Assessors and therapists will be offered an interview at a suitable time and via their preferred mode: instant message, telephone, video chat, or email. They will be asked a series of questions focusing on their ability to develop a therapeutic alliance with their participants; their views about video chat technology; exploration of any technological issues experienced; exploration of implementation barriers and facilitators; and overall reflections about how a service delivered via video chat compares with an in-person, face-to-face service. The interviews will be conducted by the first author, and if completed via telephone or video chat, the interview will be audio recorded (with permission) for qualitative analysis.

### Randomization

The process of randomly allocating participants to either the low-intensity or high-intensity treatment groups will comply with CONSORT guidelines. A block randomization design will be used to randomly allocate each participant to either the low-intensity or high-intensity therapist assistance condition throughout the trial. Random allocation will occur when a participant has met the criteria to be *stepped up* to have their Life Flex program augmented with therapist assistance. Participants will be aware of the group they have been randomly allocated to but will remain unaware of the study’s objectives. The provisional or general psychologists will not be blinded to the treatment conditions, as they will need to adhere to either the support or the therapist role.

### Sample Size Calculation

Only aggregate data will be used for the main analysis. Assuming a conservative medium effect (ie, GPower f[v] test=0.25), significance set at 5% (*P*=.05), and power at 80%, 98 cases are required to demonstrate statistical significance in the primary outcome measures. However, allowing for a 30% attrition rate [26], a total target sample size of 137 participants will be required.

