### Objectives

The purpose of this study is to present a protocol designed to evaluate various support intensities of a dMH treatment program for anxiety and depression within a mixed methods design. Therefore, the study has the following primary objectives:

To compare the efficacy of clinical outcomes (anxiety [Generalized Anxiety Disorder–7; GAD-7] and depression [Patient Health Questionnaire–9; PHQ-9] symptoms) among the 3 treatment conditions (dMH program only, low-intensity therapist assistance, and high-intensity therapist assistance), with particular focus on whether therapist-assisted support produces greater reductions in anxiety and depression severity compared with those produced by dMH program–only support.To examine the role of motivation and self-efficacy on engagement, adherence, and clinical outcomes (anxiety [GAD-7] and depression [PHQ-9] symptoms) among the 3 treatment conditions (dMH program only, low-intensity therapist assistance, and high-intensity therapist assistance) at postintervention (week 9) and follow-up (week 21) assessments, compared with those at preintervention (week 0) assessment.To explore participant and therapist experiences and satisfaction with assessment and therapist assistance delivered via video chat technology, using semistructured interviews; specific areas of focus will include the ability to develop and maintain therapeutic relationships, implementation barriers and facilitators, and identified strengths and limitations of video chat technology for conducting assessments and delivering dMH treatment.To explore therapist training and implementation experiences in the delivery of dMH interventions.To use a mixed methods analysis to examine factors affecting participant attrition in each of the treatment intensities; quantitative examination of preferences, treatment condition allocation (dMH program only, low-intensity therapist assistance, and high-intensity therapist assistance), and attrition rates will be explored; qualitative exploration of participant reasons for withdrawal and nonengagement with therapist support will also be conducted using semistructured interviews.To explore the outcomes of working alliance, health resources, and health status among the 3 treatment conditions (dMH program only, low-intensity therapist assistance, and high-intensity therapist assistance).

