## Results

Recruitment began in November 2020 and was completed at the end of March 2022. In total, 240 individuals registered for the clinical trial, of which 113 (47.1%) were assessed as eligible to commence the dMH intervention. At week 3, of the 113 participants, 73 (64.6%) met the stepped care criteria to have the dMH intervention augmented with therapist assistance, whereas 40 (35.4%) remained in the program-only condition. The results of the clinical trial are forthcoming as they have recently been accepted for publication in JMIR Publications [27].

Data will be entered, screened, and analyzed using statistical software. Intention-to-treat analysis will be used for primary outcomes, controlling for baseline differences where appropriate. The primary analysis will be conducted using 2 planned contrasts comparing a change in anxiety (GAD-7) and depression (PHQ-9) scores from preintervention assessment with those of the postintervention (week 9) and follow-up (week 21) assessments, using a mixed model repeated-measure analysis. A mixed model repeated-measure analysis is preferred owing to its ability to include participants with missing data. The study will also investigate whether reliable and clinically significant change has been achieved for participants following the recommendations of Jacobson and Traux [28]. Moderation analyses will be used to determine the role of self-efficacy and motivation in engagement and adherence and their effects on anxiety and depression outcomes in the 3 treatment conditions, and a *t* test will be used to determine the impact of preferences and treatment allocations on attrition rates.

Data obtained from open-ended questions about intervention satisfaction questionnaires and from interview questions will be transcribed verbatim from audio recordings into text and then analyzed using protocols of thematic analysis to identify common themes. Text transcripts will be read several times to identify emerging themes. Thematic analysis allows for the identification of themes that are driven by the data, using an experiential, bottom-up approach [29]. Close analysis of the data will suggest names for the themes, which are likely to represent something of meaning to participants and therapists, with direct quotes used to further illustrate meaning. Researchers will meet throughout the analysis process to review and discuss the data.

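### The stated 80% power with 98 cases appears to belong to an omnibus three-group by three-occasion test and does not carry over to the planned contrasts, least of all to low versus high, the only randomised comparison

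*Protocol article*

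**What the plan says.** The Sample Size Calculation gives one set of inputs: "Assuming a conservative medium effect (ie, GPower f[v] test=0.25", with "significance set at 5% (*P*=.05), and power at 80" per cent. From these it concludes that "98 cases are required to demonstrate statistical significance in the primary outcome measures" and, "allowing for a 30% attrition rate [26], a total target sample size of 137 participants will be required". It does not state the test, the number of groups or occasions, the contrast, or the share of participants expected to step up.

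The first item under Objectives compares outcomes "among the 3 treatment conditions (dMH program only, low-intensity therapist assistance, and high-intensity therapist assistance), with particular focus on whether therapist-assisted support" reduces symptoms more than the program alone. Under Results, "The primary analysis will be conducted using 2 planned contrasts", on change from week 0 to weeks 9 and 21 in a mixed model, controlling for baseline differences where appropriate. The article does not define which groups the two contrasts compare.

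The Randomization section says that blocks will be used to "randomly allocate each participant to either the low-intensity or high-intensity therapist assistance condition", and that this happens only once someone meets the step-up criteria. The Life Flex Program–Only Condition section leaves in program-only those who improve or engage early, so that group is not formed by randomisation. Results reports that "of the 113 participants, 73 (64.6%) met the stepped care criteria to have the dMH intervention augmented with therapist assistance"; the other 40 stayed in program-only.

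**The concern.** The 80% is attached to the primary outcomes without limit, so a reader will take it to cover whatever comparison is reported on GAD-7 and PHQ-9. A figure for an omnibus interaction across three groups does not transfer to a contrast between two of them. It transfers least to low versus high, which leaves out everyone who stays in program-only.

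This matters because of how the result is to be used. Under Principal Findings in the Discussion, similar outcomes in the low and high conditions would be taken as support for low-intensity delivery in the community. If power for that comparison is well under 80%, a non-significant difference is weak evidence of similarity, yet the article invites the reader to think that an adequately powered test stands behind it.

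**Working it through.** **Reproducing 98.** From the article: f(V) = 0.25, level 0.05, power 0.80. Inferred: k = 3 groups (the three conditions) and m = 3 occasions (weeks 0, 9, 21). The notation f(V) points to the repeated-measures MANOVA interaction (Pillai) in the software named:

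- s = min(k−1, m−1) = 2
- df1 = (k−1)(m−1) = 4
- df2 = s(N − k − (m−1) + s) = 2(98 − 3 − 2 + 2) = 190
- λ = N·s·f(V)² = 98 × 2 × 0.0625 = 12.25
- Power from the noncentral F = 0.8005, and 98 is the smallest N that reaches 0.80.

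The other layouts tried under the same convention give: 2×2, 128; 2×3, 158; 3×2, 158; 3×4, 113; 3×5, 125. Only 3×3 gives 98. The target of 137 is 98 × 1.4 = 137.2.

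**Low versus high: inputs.** For two groups and two occasions, f(V) = 0.25 corresponds to a standardised difference d = 2 × 0.25 = 0.5. Allocation 1:1 is assumed. Numbers analysed:

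- 63 = 98 × 73/113
- 73 = everyone stepped up, no attrition
- 51 = 73 × 0.7, the plan's own 30% attrition
- 98 = a limiting case in which every analysed participant was randomised

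**Formulas.** Two-sided 5% noncentral t with noncentrality (d/√v) × √N/2, where v is the residual variance relative to the outcome variance:

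- Unadjusted, one time point: v = 1, df = N − 2.
- Baseline-adjusted, one time point: v = 1 − r², df = N − 3. At r = 0.5, v = 0.75.
- Baseline-adjusted mean of weeks 9 and 21, all correlations 0.5: v = (1 + 0.5)/2 − 0.5² = 0.5, df = N − 3.

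Example: N = 73 unadjusted has noncentrality 0.5 × 8.544/2 = 2.136, giving power 0.56.

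| Analysed | Unadjusted | Adjusted, r = 0.5 | Adjusted, weeks 9 and 21 averaged |
|---|---|---|---|
| 51 | 42% | 52% | 70% |
| 63 | 50% | 62% | 79% |
| 73 | 56% | 68% | 85% |
| 98 | 69% | 81% | 93% |

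The article gives no value for r. At one time point with adjustment, r from 0.3 to 0.7 gives 45–69% (N = 51), 53–78% (N = 63) and 60–84% (N = 73).

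**Detectable difference at 80% power**, solving the same formula for d: unadjusted, 0.66 SD with 73 and 0.80 SD with 51. At r = 0.5, multiply by √0.75 = 0.866: 0.58 and 0.69 SD.

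Unadjusted, 80% power at d = 0.5 needs 128 analysed, the 2×2 figure above.

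**The case against.** The strongest reply has four parts.

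- **The 98 is not miscalculated.** This stands. It reproduces exactly for a layout that fits the three conditions and the three primary time points. A reader might infer an arithmetic error; there is none. The fault is in what the figure is said to cover. The 3×3 basis is itself an inference, because the article names no test, so the sponsor should confirm it.
- **Low versus high is not the lead question.** Objectives and Principal Findings put therapist assistance against program-only first and say that low versus high will also be evaluated. That is fair, but the 80% does not transfer to the lead comparison either: at d = 0.5 with 63 against 35, the noncentrality is 0.5/√(1/63 + 1/35) = 2.37 and unadjusted power is 65%. That comparison is also not randomised, a separate problem that no restated power figure cures.
- **The observed 73 of 113 was unknown at planning.** This stands too. It cannot show that the planning figure was wrong when set. What can be said is that no step-up share was planned for.
- **Power depends on the analysis.** This also stands. Results allows baseline adjustment, and with a high correlation or averaging over weeks 9 and 21 power approaches or passes 80%. A reader might infer that low versus high was a coin toss, or quote 39%, 45% and 32% for 63, 73 and 51 analysed. Those three figures come from a two-degree-of-freedom omnibus test over three occasions, which the plan does not use, and so understate a single contrast.

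Nor is f(V) = 0.25 the same effect in both layouts. Placing the whole 3×3 Pillai V (2 × 0.0625/1.0625 = 0.118) on low versus high gives f(V) = √(0.118/0.882) = 0.365, or d = 0.73, with two-occasion power of 81% at 63 and 87% at 73. That is a larger difference than d = 0.5.

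**Conclusion.** The point holds in a limited form. The unqualified 80% for the primary outcomes appears to be the power of a 3×3 omnibus interaction over 98 analysed participants in all three conditions, and it does not describe the two planned contrasts. For low versus high at d = 0.5, power is about 42–56% unadjusted and 52–68% with baseline adjustment at r = 0.5, for 51 to 73 analysed. At that correlation it reaches about 70–85% only if weeks 9 and 21 are also averaged, which the article does not state. A correlation near 0.7 would raise the single-time-point figures to 69–84%.

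These results rest on 1:1 allocation, d = 0.5 as the two-group reading of f(V) = 0.25, and assumed correlations. It might be inferred that 80% is out of reach at any step-up share. That holds only for the unadjusted analysis, where even 98 randomised gives 69%; with adjustment at r = 0.5 it would be 81%. Nor do the documents support calling the comparison hopeless. They support saying that its power is unstated, probably below 80% at the numbers available, and dependent on an analysis that the article does not fix.

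**What to change.** In the Sample Size Calculation, name the test, number of groups and number of occasions behind 98, and limit the 80% to that test. Add the power and detectable difference for low versus high at the 73 randomised and at about 51 after 30% attrition: 0.66 to 0.80 SD unadjusted, or 0.58 to 0.69 SD at an assumed r of 0.5. State the assumed analysis (single time point or average, adjusted or not) and the correlation.

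Where similarity of low and high is interpreted, report the estimate with its confidence interval, and do not present a non-significant difference as adequately powered evidence of similarity.

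Recruitment is complete, so this changes reporting only. It needs no added participants; the cost is a less favourable stated figure.

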**Methods:**

Australian adults (N=137) with symptoms or a diagnosis of anxiety or depression will be screened for eligibility and given access to the 8-module Life Flex dMH treatment program. On day 15, participants who meet the augmentation criteria will be *stepped up* via block randomization to receive therapist assistance delivered via video chat for either 10 minutes (low intensity) or 50 minutes (high intensity) per week. This adaptive trial will implement a mixed methods design, with outcomes assessed before the intervention (week 0), during the intervention (weeks 3 and 6), after the intervention (week 9), and at the 3-month follow-up (week 21).

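### The target of 137 falls slightly short of the stated 30% attrition allowance (140 is needed), and the 98/137/80% statement is not reconciled with the 113 who started

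*Protocol article*

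**What the plan says.** The Sample Size Calculation section of the protocol article gives the effect size as "Assuming a conservative medium effect (ie, GPower f[v] test=0.25" and continues: "significance set at 5% (*P*=.05), and power at 80%, 98 cases are required". It then inflates for loss: "allowing for a 30% attrition rate [26], a total target sample size of 137 participants will be required". The Methods paragraph of the abstract carries the same N=137.

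The Results section reports that recruitment is finished: of 240 people who registered, "113 (47.1%) were assessed as eligible to commence the dMH intervention". At week 3, 73 of these met the step-up criteria and 40 stayed on the program alone. The section does not compare 113 with 137, restate the power or give the attrition observed. It plans an intention-to-treat mixed model for repeated measures, chosen because it can keep participants with missing data.

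In the Discussion, Principal Findings says that similar outcomes under low and high assistance would support low-intensity delivery. Limitations says only that recruitment and engagement may prove difficult, although recruitment had already closed.

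**The concern.** There are two separate issues.

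- **The inflation for attrition.** The target does not follow from the two figures beside it. Dividing 98 by the retained fraction does not give 137.
- **The number who started.** The article publishes both the planned size with its 80% power and a final intake 24 below target (137 − 113), and does not connect them.

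What is at stake is how a null result is read. The Discussion intends to draw a practical conclusion if low and high assistance turn out similar. A reader who takes the 80% at face value will give a non-significant difference more weight than the recruited sample may support.

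**Working it through.** **Inputs.** From Sample Size Calculation: f(V) = 0.25, alpha = 0.05, power 0.80, 98 cases, 30% attrition, target 137. From Objectives: 3 treatment conditions. From Results: 113 starters, with contrasts that use the pre-intervention, week 9 and week 21 assessments. The article does not say how many measurements entered the calculation; 3 is inferred from those contrasts.

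**Step 1: reproduce 98.** Take the group-by-time interaction in a repeated-measures MANOVA (Pillai trace) with k = 3 groups and m = 3 measurements.

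- p = m − 1 = 2, q = k − 1 = 2, s = min(p, q) = 2
- numerator df = p × q = 4
- denominator df = s(N − k − p + s) = 2(N − 3)
- noncentrality λ = f(V)² × s × N = 0.0625 × 2 × N = 0.125N

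At N = 98, λ = 12.25 with 4 and 190 df, and power is 0.8005. This is the smallest N that reaches 0.80, so the plan's figure is matched exactly. With 4 or 5 measurements the same method needs 113 or 125, which supports the inference of 3. (That this 113 equals the number of starters is coincidence.)

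**Step 2: the attrition allowance.**

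- Required: 98 / (1 − 0.30) = 140
- What 137 leaves at 30%: 137 × 0.70 = 95.9
- Attrition that 137 covers: 1 − 98/137 = 28.5%
- Possible source of 137: 98 × 1.4 = 137.2. Multiplying by 1.3 would give 127.4, so that is not where it came from.

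Power is 0.786 at 95 completers and 0.791 at 96, against 0.80 planned. The shortfall is 3 participants, or about 1 point of power.

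**Step 3: the 113 who started.** Same test and same effect size:

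| Attrition | Completers from 113 | Power |
|---|---|---|
| 0% | 113 | 0.86 |
| 13% | 98 (98.3) | 0.80 |
| 20% | 90 (90.4) | 0.76 |
| 30% | 79 (79.1) | 0.69 |

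The break-even attrition is 1 − 98/113 = 13.3%. At the plan's own 30%, the type II error is about 31% instead of 20%.

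**The case against.** The strongest reply has four parts.

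- **The slip is trivial.** Three participants and one point of power do not defeat an 80% design. This stands. Alone, it would be a minor note.
- **The 69% describes an analysis that is not planned.** It assumes 30% attrition, which the article does not report as having occurred, and analyses completers only, whereas the mixed model keeps partial records. This also stands. A reader might infer that the trial failed to deliver 80% power, but the document does not support that as a fact. With attrition at or below about 13% the 98 cases would be there. At 30% attrition, partial records add some information, so power under the mixed model would lie between 69% and 86%.
- **Falling short in recruitment is an outcome, not a planning error.** The figure of 113 is openly reported, and the results are in a separate paper not seen here. That is fair, and the planning calculation is not made wrong by it. But this article states both sets of figures after recruitment closed, and its own text leaves them unreconciled.
- **The abstract is consistent.** A reader might infer that it misdescribes 137 as the number screened, from "Australian adults (N=137) with symptoms or a diagnosis of anxiety or depression will be screened for eligibility". The sentence goes on to say that these adults are also given access to the program, so it can be read as the enrolment target and agrees with the sample size section. No point is made of it.

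**Conclusion.** The point holds in two parts of unequal weight. First, 137 is not the size that 30% attrition on 98 cases requires. The figure is 140; the error is about 2% and costs about 1 point of power. Second, and more important, the 98/137/80% statement stands unqualified beside a final intake of 113, for which the plan's own attrition assumption implies about 79 completers and about 69% power.

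The second part is conditional. It rests on the inferred three measurements, on f(V) = 0.25 and on attrition that the article does not report. The supportable statement is a range from about 69% (30% attrition, completers only) to about 86% (no loss), crossing 80% at about 13% attrition. Attrition above 30% would allow lower values. All these figures concern the three-group interaction. They do not give the power to separate low from high assistance, which involves only the 73 who were stepped up, so neither they nor the stated 80% should be carried over to that comparison.

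**What to change.** Correct the text only. No further enrolment and no change to the analysis is asked for.

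1. In Sample Size Calculation, keep 137 as the historical target, and note that 30% attrition on 98 cases needed 140 and that 137 covers about 28.5%. Rewriting the target to 140 after recruitment closed would misstate what was planned.
2. Name the test, number of groups and number of measurements behind the 98, so that the three measurements need not be inferred.
3. In Results, state that 113 started against a target of 137, and give power conditionally: about 69% at 30% attrition, 80% at about 13%, and 86% with no loss. Add that the mixed model retains partial data and, at 30% attrition, falls between 69% and 86%.
4. In Principal Findings or Limitations, add that a non-significant difference, including low versus high assistance, is not to be read as if backed by 80% power.

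The cost is a few sentences and a power statement that may be less favourable than the published one.
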